### Withdrawal and dropout criteria

The participants can withdraw their consent at any point during the trial. If the participant becomes unstable during the surgery, the primary investigator can exclude the participant from the trial for the safety of the participant. This will be effectuated in case of:

- Severe intra-abdominal bleeding
- Allergic reaction to general anaesthesia
- Other severe complications during surgery

A participant has concluded the trial when the 30-day postoperative follow-up has been conducted.

The trial will be stopped if severe adverse effects or severe complications, which are not expected, arise from the trial treatment. This will be decided by the sponsor.

### **Other drugs during the trial**

The participants can receive any pain medication (paracetamol, ibuprofen, tramadol, or morphine) necessary before or after the surgery. Further, the patients can receive intravenous fluids without restrictions and the necessary thrombosis prophylaxis. In addition, medication necessary for anaesthesia and nausea can be administered without restrictions.

### **Measurements**

Primary outcome:

- Preoperatively, white blood cell counts at admission (baseline) compared with white blood cell counts 4 hours  $\pm$  30 minutes postoperatively are analysed by Department of Clinical Biochemistry, Herlev Hospital according to their usual standards. The blood samples are destroyed after analysis. A toxic effect defined by a drop below the reference range.

Secondary outcomes:

- Preoperative biochemical markers are analysed at admission (baseline) and 4 hours  $\pm$  30 minutes postoperatively by Department of Clinical Biochemistry, Herlev Hospital according to their usual standards. These include a standard panel of blood samples, which are seen in Supplements, Table 3. The blood samples are destroyed after analysis. This requires a total of 20.5 ml blood.
- Vital signs (pulse, blood pressure, temperature, frequency of respiration, and SAT) are measured perioperatively (baseline, 5 minutes, 10 minutes

and 15 minutes after the trial treatment has been administered) and postoperatively (4 and 12 hours  $\pm$  30 minutes after the trial treatment has been administered).

- Length of stay in hours postoperatively.
- Side effects: evaluated through an objective examination and questions about changes 12 hours  $\pm$  30 minutes and 10 days postoperatively  $\pm$  1 day.
- Adverse events: registered from the surgery until 30 days postoperatively through medical records and contact with the participant by telephone.

## **Statistics**

The number of patients needed for the trial is not based on a power calculation. This trial is a pilot observational safety trial of the intraperitoneal administration of fosfomycin, metronidazole, and GM-CSF. We have decided that 14 patients are needed to collect a minimum of information about the safety of the intraperitoneal treatment.

Continuous numerical data will be reported as mean and standard deviation if normally distributed. If not normally distributed, continuous numerical data will be reported as median and percentiles. We will analyse data with both parametric and non-parametric statistics depending on the distribution of the data. A p-value  $<0.05$  is considered significant.

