### **Secondary outcomes**

Repeated biochemical markers (including a white blood cell differential count, inflammation marker C-reactive protein (CRP), kidney function tests, liver

function tests, and electrolytes), vital signs (blood pressure, pulse, frequency of respiration, peripheral saturation (SAT), and temperature,), length of stay, side effects, and adverse events until 30 days after surgery.

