## **Design**

An open-label, phase II, pilot study of 14 participants.

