## **Trial participants**

Inclusion criteria:

- Men  $\geq 18$  years old
- Suspicion of acute appendicitis and planned for diagnostic laparoscopy and eventual appendectomy
- Written informed consent after written and verbal information

Exclusion criteria:

- Cannot understand, read or speak Danish
- Previous allergic reaction to fosfomycin, metronidazole, or GM-CSF
- Perforated appendicitis (diagnosed either during surgery or at a preoperative computer tomography (CT) scan)
- Diagnostic laparoscopy revealing normal appendix not requiring an appendectomy
- Other intra-abdominal pathology requiring surgical intervention (diagnosed either during surgery or at a preoperative CT-scan)
- Known renal or hepatic disease or biochemical evidence at the time of admission
- Known autoimmune disease or other chronic inflammation
- Known hematologic disease or cancer
- Previous abdominal surgery (either laparoscopic or open surgery)
- Daily use or use of medication one week prior to or during the trial period apart from painkillers such as paracetamol, ibuprofen, tramadol, and morphine as well as drugs needed for anaesthesia, thrombosis prophylaxis, and nausea. Limitations for antibiotics are defined below

- Use of other antimicrobial agents than the trial treatment one month before until 24 hours after the trial treatment
- Participant in another drug trial one month prior to the date of the surgery
- Body mass index  $\geq 35$  kg/m^2
- Weekly intake of alcohol >14 units, where one unit corresponds to 12 g alcohol

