### Side effects of fosfomycin

Fosfomycin is generally well tolerated. A surveillance study of more than 35,000 patients receiving orally administered fosfomycin reported side effects in less than 3.5% of the patients. The most common side effects were gastrointestinal disturbances such as vomiting and abdominal pain, which are common side effects of many antimicrobial agents. Further, after intravenous administration of doses of 4 g fosfomycin 4 times a day in 11 critically ill patients, no adverse events was experienced. Diarrhoea was reported in one child after intravenous doses of 200 mg/kg fosfomycin were administered in 23 children suffering from osteomyelitis. Other studies reported high sodium, which is the dose limiting factor, and more seldom: allergic reactions, headache, rhinitis, vaginitis, and

phlebitis. In pharmacokinetic studies where fosfomycin was administered intraperitoneally adverse events were not reported.

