### **Side effects of GM-CSF**

GM-CSF has overall been reported well tolerated regardless of route of administration. GM-CSF administered intravenously in an RCT in patients requiring admission to the intensive care unit reported reversible oliguria as the only side effect. A pharmacokinetic study of escalating doses (0.3, 1, 3, 10, 15, and 20 µg/kg/day) in patients with advanced malignancy and/or neutropenia reported the following most common adverse clinical effects: 71% bone pain, 62% lethargy/malaise, 38% rash and/or pruritus, 38% first dose reaction, 29% fever, 24% fever and rigors, 14% weight dose gain, 10% marginal keratitis, 10% nasal congestion, and 10% pericardial pain. Adverse effects such as fever, pericarditis, and liver abnormalities were not seen in

patients receiving  $<10 \mu\text{g/kg}$ . Also transient leukopenia was seen after intravenous administration. The first dose reaction is characterised by either symptomatic hypotension, hypoxia or both and at least two other common symptoms (flushing sensation, muscular or bone aches, throbbing lumbar back pain, dyspnoea, nausea and vomiting, rigor or fever, and involuntary leg spasms). This happened within  $60 \pm 40$  minutes after intravenous injection or infusion. Subcutaneous administration in patients with sepsis resulted in no side effects. However, the first dose reaction was associated with high serum concentrations and an intravenous administration route. Another pharmacokinetic study reported bone pain, chills/rigors, dyspnoea, fever, serositis and thrombosis after intravenous administration of escalating doses of GM-CSF of 1, 2, 4, or  $8 \mu\text{g/kg/day}$ . One pharmacokinetic study did not report on adverse effects.

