An RCT reported the following adverse reactions after a dose of  $3 \mu\text{g/kg/day}$  GM-CSF administered subcutaneously to patients with abdominal sepsis: thrombocytopenia, generalised rash, nausea, deep vein thrombosis, and superficial phlebitis. A pharmacokinetic dose escalating study reported the following adverse effects: fever, bone pain, arthralgia/myalgia, skin reaction, increased liver enzymes, thrombocytopenia and pericarditis after subcutaneously administered doses of 0.3, 1, 3, 10, 15, 20, or  $30 \mu\text{g/kg/day}$  to patients with advanced malignancy. Pericarditis occurred only after high doses. The transient leukopenia seen after intravenous administration arose later after subcutaneous administration. One pharmacokinetic study did not report on adverse effects.

Only a transitory flu-like syndrome was reported after doses of  $68 \mu\text{g/day}$  GM-CSF administered intraperitoneally in patients undergoing peritoneal dialysis. A pharmacokinetic study reported fever and serositis after intraperitoneal administration of escalating doses of 1, 2, 4, or  $8 \mu\text{g/kg/day}$  in patients with advanced intraperitoneal malignancy. This study, which also administered GM-CSF intravenously, noted that first dose reaction was seen only after intravenous and not intraperitoneal administration.

We expect fewer and less serious side effects of GM-CSF than described in the above studies because of the intraperitoneal administration route and the low dose that has been chosen.

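### The secondary laboratory safety outcomes are tested only as group averages, which in 14 men would usually miss a marked but silent change in one to three of them

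*Protocol*

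**What the plan says.** The main trial is described under Design as "An open-label, phase II, pilot study of 14 participants". Its Statistics section says "The number of patients needed for the trial is not based on a power calculation". For analysis it says "Continuous numerical data will be reported as mean and standard deviation if normally distributed", with median and percentiles otherwise. Parametric or non-parametric methods follow the distribution, and p<0.05 counts as significant. It names no specific test and no percentiles, and does not say whether tests are one- or two-sided.

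Besides repeated biochemical markers, the secondary outcomes include "function tests, and electrolytes), vital signs (blood pressure, pulse, frequency of respiration, peripheral saturation (SAT), and temperature,), length of stay, side effects, and adverse events". Under Measurements the blood panel is taken at admission and again at 4 hours. Table 3 in the Supplements prints a reference range for each marker on the panel, including sodium, thrombocytes and alanine transaminase.

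A per-participant criterion, a fall below the lower reference limit, is set under Primary outcome and repeated under Measurements for the white cell count. No section extends such a reading to the other markers.

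The side-effect sections name harms that match measured markers. For fosfomycin: "Other studies reported high sodium, which is the dose limiting factor". For subcutaneous GM-CSF in a dose-escalation study: "increased liver enzymes, thrombocytopenia and pericarditis".

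**The concern.** A drug harm of this kind appears in some individuals and not in others. A mean, a median or a paired test asks whether the typical man changed, which is a different question. The protocol asks the individual question for white cells and then, for sodium, liver enzymes and platelets, fixes an analysis that does not ask it, although the limits needed are already printed in Table 3.

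At stake is false reassurance in a trial whose main aim is safety. The 4-hour panel is an extra sample beyond usual care, and the Statistics section is the only place that says how it will be analysed. If one or two men had a marked rise in sodium or fall in platelets without symptoms, the planned analysis could still report no significant change.

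**Working it through.** **Inputs from the protocol.** n = 14 in a single group, each man compared with his own admission value; significance at p<0.05. The sample size comes from no calculation, so there is no figure of the plan's own to reproduce.

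**Assumptions.** Two-sided tests. Within-person changes are normal with mean zero and SD 1, because no variability is given. Of the 14 men, r have an added shift of d SDs.

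**Step 1: limiting case of the paired t-test.** Suppose r men share the same very large change d and the others do not change.

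- Mean change = rd/n
- Variance of the changes = d² × r(n−r) / [n(n−1)]
- t = mean / √(variance/n) = √[r(n−1)/(n−r)] = √[13r/(14−r)], in which d cancels

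The critical value is t(0.975, 13) = 2.160.

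| Men affected | t in the limit | two-sided p |
|---|---|---|
| 1 | √(13/13) = 1.00 | 0.34 |
| 2 | √(26/12) = 1.47 | 0.16 |
| 3 | √(39/11) = 1.88 | 0.082 |
| 4 | √(52/10) = 2.28 | 0.040 |

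In this idealised case, significance needs about four affected men, however large the change. With a one-sided test three men would just suffice (p = 0.041), but one or two would not.

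**Step 2: with ordinary variation in all men.** Simulated trials of 14 men with shifts of 3, 5 and 8 SD give the chance of p<0.05 below. The last column uses a Shapiro-Wilk check at 0.05 (an assumption) to choose between the t-test and Wilcoxon, which is closest to the protocol's rule of letting the distribution decide.

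| Men affected | t-test always | Wilcoxon always | Chosen by distribution |
|---|---|---|---|
| 1 | about 0.5–4% | about 5% | about 4–5% |
| 2 | about 2–9% | about 8–9% | about 8–10% |
| 3 | about 14–19% | about 15–17% | about 16–18% |

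With one affected man, detection is no better than the 5% false-positive rate.

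**Step 3: what the summaries show.** At a shift of 5 SD the median moves by about 0.10, 0.21 and 0.35 SD for one, two and three men. The SD rises from 0.98 to 1.65, 2.06 and 2.33. The spread therefore carries a trace, but does not say how many men crossed a limit.

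**Step 4: what a count shows (exact 95% intervals).**

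- 0/14: upper limit 23.2%
- 1/14 = 7.1% (0.2–33.9%)
- 2/14 = 14.3% (1.8–42.8%)
- 3/14 = 21.4% (4.7–50.8%)

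A single case is visible at once. The interval for zero cases also shows how little 14 men can exclude.

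**The case against.** **Shift tables and listings belong in a statistical analysis plan.** That is fair, and their absence from the protocol is no finding. The point rests on what the Statistics section does fix: a group summary with a significance rule, and nothing per man beyond white cells. It does not say that a non-significant result will be read as safe; the criticism is that the stated analysis supports little else.

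**Individual harms have other routes.** This largely stands for vital signs. A reader might infer that falls in blood pressure or saturation would go unnoticed. The documents do not support that. The protocol describes the reaction as follows: "The first dose reaction is characterised by either symptomatic hypotension, hypoxia or both", together with other symptoms. Vital signs are noted per participant at 5, 10 and 15 minutes and at 4 and 12 hours (Trial course). Examinations follow at 12 hours and 10 days, adverse events are collected to day 30, and complications are attended by a doctor. A silent laboratory change is different: Reporting of side effects defines an event as a sign, symptom or disease and does not say that an abnormal value counts.

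**A larger harm might seem to make significance less likely.** That holds for one affected man if a t-test is always used. The protocol lets the distribution decide, and then detection is low but flat across 3 to 8 SD.

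**False positives from dozens of comparisons.** The protocol does not say that every marker and time point will be tested, so no count of expected chance findings is claimed.

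**The named harms come from other settings.** This is true. The liver-enzyme and platelet quote concerns subcutaneous doses up to 30 µg/kg/day, liver abnormalities were not seen below 10 µg/kg, and the intraperitoneal fosfomycin studies reported no adverse events. This lowers the expected frequency. It does not make a group average the right way to look.

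**Counting has its own false alarms.** This is also true. If the ranges are central 95% intervals (an assumption), 25 secondary rows × 14 men × 0.05 = 17.5 values out of range at one time point by chance. How many are new depends on within-person correlation.

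**Conclusion.** The point holds for the secondary laboratory outcomes, chiefly asymptomatic changes in sodium, liver enzymes and platelets. The stated analysis would miss a marked change in one to three of 14 men in roughly 95%, 90% and 83% of trials respectively. This assumes a two-sided test, normal within-person changes, shifts of 3 to 8 SD and no average change in the remaining men. Detection is low, not nil, and the SD and percentiles may hint at an outlier. Blood pressure and saturation are a minor part of the point, for the reasons above.

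One further inference should be avoided. The exclusion "Known renal or hepatic disease or biochemical evidence at the time of admission" might suggest that any abnormal kidney or liver value at 4 hours is new. It excludes evidence of disease, not every out-of-range value, so each 4-hour result must be read against that man's own admission value.

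This is worth changing because a better reading of data already collected is available at little cost. It does not invalidate the trial or its primary outcome.

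**What to change.** In the main trial's Statistics section:

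- For each Table 3 marker other than the white cell count, add a shift table from admission to 4 hours (below, within, above range). Report new out-of-range values as n/14 with an exact 95% confidence interval.
- List each participant's most extreme post-treatment value for each vital sign. The protocol prints no limits for these, so a listing is enough.
- Keep mean and SD, or median and percentiles, as description. State that p≥0.05 for a group change will not be taken as evidence of safety.

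Verify the Table 3 limits first. The INR row gives 2,0–3,0, although INR is a ratio to normal plasma and a normal range that leaves out 1 needs checking. Free calcium and calcium carry the same range, 1,18–1,32 mmol/l. C-reactive protein is a secondary outcome but has no row in the table as it can be read here.

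The cost is a few sentences, one table and one listing, with no new samples, visits or participants. The intervals will be wide. Some out-of-range values will reflect surgery, fluids or chance, and without a control group these cannot be separated from a drug effect. A count also sees only what the 4-hour sample contains.

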### **Primary outcome**

The safety of intraperitoneal administration is evaluated through the white blood cell counts 4 hours postoperatively. A toxic effect is defined by a drop below the lower reference range.

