## Summary

**Background:** In secondary peritonitis, bacteria that have escaped from abdominal organs cause an infection in the abdominal cavity. Peritonitis can have long-term consequences for the patients. The severity of the disease depends on the extent of inflammation. Current treatment practice is surgical intervention (source control) in combination with the administration of intravenous antibiotics. We wish to administer two antimicrobial agents: fosfomycin and metronidazole, together with granulocyte-macrophage colony-stimulating factor (GM-CSF), which stimulates the function of macrophages. The surgical intervention is kept. The trial drugs are administered at the site of the disease: intraperitoneal administration. Thereby the abdominal cavity receives highest concentration of the drugs. Furthermore, in addition to the antimicrobial treatment, the patient's local immune defence is stimulated by GM-CSF.

This pilot trial will be conducted in otherwise healthy patients suffering from uncomplicated appendicitis. The administration of the trial treatment demands an intra-abdominal access, which is routinely established during surgery. The trial will consist a main trial: Safety and a sub-trial: Pharmacokinetics that involve and recruit from the same trial population.

**Main trial: Safety:** The primary objective is to investigate if intraperitoneal administration of fosfomycin, metronidazole, and GM-CSF is safe, on the basis of white blood cell counts four hours after the surgery. Secondary objectives are measurements of vital signs at baseline, 5, 10 and 15 minutes and again 4 and 12 hours after administration of the trial treatment, length of stay and side effects evaluated by an objective examination and questions about changes 12 hours and 10 days after administration of the trial treatment. A follow-up is conducted 30 days after the surgery. Fourteen otherwise healthy males  $\geq 18$  years diagnosed with uncomplicated appendicitis are needed to complete the main trial.

**Sub trial: Pharmacokinetics:** The primary objective is to investigate the plasma concentrations of fosfomycin after intraperitoneal administration over time. Secondary objectives are investigations of metronidazole concentrations after intraperitoneal administration over time and microbiologic investigations of

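### The only safety criterion for the primary outcome is a per-participant threshold, but the Statistics section commits to continuous summaries and a p<0.05 rule that do not evaluate it

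*Protocol*

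**What the plan says.** All references are to the Protocol, main trial on safety.

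- **Outcome and criterion (Primary outcome).** "The safety of intraperitoneal administration is evaluated through the white blood cell counts 4 hours postoperatively". The next sentence gives the rule: "A toxic effect is defined by a drop below the lower reference range". Table 3 in the Supplements puts the WBC reference range at 3.5 to 8.8 × 10⁹/l, so the limit is 3.5.
- **Comparison (Measurements, primary outcome).** The bullet refers to "white blood cell counts at admission (baseline) compared with white blood cell counts 4 hours", within 30 minutes either way, and repeats the toxicity threshold.
- **Objective (Summary).** The aim is to find out whether the treatment "is safe, on the basis of white blood cell counts four hours after the surgery".
- **Design.** "An open-label, phase II, pilot study of 14 participants". No control group is described.
- **Analysis (Statistics).** Continuous data are summarised by mean and standard deviation, or by median and percentiles if not normal. Then: "We will analyse data with both parametric and non-parametric statistics depending on the distribution of the data". A p-value below 0.05 counts as significant. The section says that 14 was not derived from a power calculation and is meant to give a minimum of safety information.

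The Statistics section does not mention the number or proportion of participants with a toxic effect, does not say which hypothesis the p<0.05 rule tests, and does not connect any result to the word safe.

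**The concern.** The criterion and the analysis concern different quantities. The criterion asks how many of the treated participants had a 4-hour count below 3.5. The analysis describes the centre and spread of a continuous variable and offers a significance test of something unspecified. A mean can be well inside the reference range while individuals are below it, and it can shift markedly while nobody is.

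If the p<0.05 rule is applied to the one comparison named for the primary outcome, there is also a problem of attribution. Between the admission sample and the 4-hour sample lie the further course of the appendicitis, anaesthesia, unrestricted intravenous fluids, the operation, removal of the appendix, and three trial drugs given together. With no control group, the change cannot be divided among these. A significant change would not be toxicity, and a non-significant one would not be safety.

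At stake is what the trial can claim. The Summary sets out to learn whether the treatment is safe, and the plan gives no route from 14 counts to a statement of that kind.

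**Working it through.** **Plan's own figure.** The only design number is 14, and the Protocol says that it is not calculated. There is nothing to reproduce; the check is what 14 participants can say about the stated criterion.

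**Inputs.** n = 14 (Design); toxic effect = 4-hour WBC below 3.5 × 10⁹/l (Primary outcome, Table 3). Assumed: all 14 are treated and have a 4-hour count, participants are independent, and the interval is two-sided 95%.

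**Exact (Clopper-Pearson) interval for x of n.** Lower limit = 2.5% quantile of Beta(x, n−x+1), or 0 if x = 0. Upper limit = 97.5% quantile of Beta(x+1, n−x). For x = 0 the upper limit reduces to 1 − 0.025^(1/14) = 0.2316.

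| Toxic / treated | 95% interval |
|---|---|
| 0/14 | 0% to 23.2% |
| 1/14 | 0.2% to 33.9% |
| 2/14 | 1.8% to 42.8% |

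With a one-sided 95% limit, 0/14 gives 1 − 0.05^(1/14) = 19.3%.

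**Chance of seeing no toxic effect when the true rate is p:** (1 − p)^14.

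- p = 5%: 0.95^14 = 48.8%
- p = 10%: 0.90^14 = 22.9%
- p = 20%: 0.80^14 = 4.4%

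**Can a before-after test stand in for the criterion?** The Protocol gives no expected WBC values, so this step is only an illustration. It assumes bivariate normal counts (× 10⁹/l), a two-sided paired t-test at 0.05 (a test the Protocol does not name) and 20,000 simulated trials of 14 per row.

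| Admission mean (SD) | 4 h mean (SD) | Correlation | p<0.05 | At least one below 3.5 | p<0.05, none below | p≥0.05, at least one below |
|---|---|---|---|---|---|---|
| 14 (4) | 14 (4) | 0.6 | 5.0% | 6.0% | 4.7% | 5.7% |
| 14 (4) | 11 (3) | 0.6 | 89.1% | 8.5% | 81.5% | 0.9% |
| 14 (4) | 10 (2.5) | 0.5 | 97.6% | 6.6% | 91.2% | 0.2% |
| 14 (4) | 12 (6) | 0.3 | 20.1% | 68.0% | 4.1% | 52.0% |
| 9 (3) | 8.5 (3.5) | 0.5 | 8.2% | 67.2% | 1.9% | 61.0% |

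The percentages depend on the assumed values and are not predictions for this trial. They show only that test and criterion can disagree in both directions, because one concerns the mean and the other the lower tail.

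**The case against.** The strongest reply has four parts.

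1. **This is a declared pilot.** The Protocol states that there was no power calculation and claims only a minimum of information. Laboratory values, vital signs, side effects and 30-day adverse events also bear on safety. This stands: 14 is not an error, and neither is imprecision as such.
2. **WBC is continuous.** The primary outcome is the count itself with a threshold attached, so means and medians are legitimate. This stands for description, and the fix keeps them. The threshold is still the only criterion of safety given for that outcome.
3. **Silence is not a prohibition, and an SAP may exist.** Saying how continuous data will be reported does not forbid counting participants below 3.5, and the count follows from the definition. The interval method could indeed be left to an SAP. The point does not rest on that omission: the Protocol commits to a significance rule and to an objective about safety, and the rule does not serve the objective.
4. **No paired test is named.** Correct. That p<0.05 applies to admission versus 4 hours is inferred from reading Measurements and Statistics together.

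A reader might go further and infer that the trial would declare the treatment safe because p exceeds 0.05. The text does not support this: no section ties a p-value to safety, and toxicity is defined by the threshold alone. Nor does it support a count of chance findings across the secondary measurements, since no section says that each analyte and time point will be tested, or a figure for how often a normality check would mislead, since no such check is named.

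**Conclusion.** The point holds in this limited form. The Protocol defines toxicity by a per-participant threshold and asks whether the treatment is safe, but its Statistics section commits to summaries and a significance rule that do not evaluate the threshold. If that rule is applied to the only comparison named, an uncontrolled change from admission to 4 hours, the p-value cannot be attributed to the drugs.

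The size of what is left unsaid is clear. The best possible result, 0/14, leaves true toxicity rates up to 23.2% compatible, and a true rate of 10% would produce that result with probability 23%. These figures rest on 14 evaluable, independent participants and an exact two-sided 95% interval; they need no assumption about WBC values.

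The change is worth making but the flaw is not fatal. The planned data contain everything needed for the right analysis, and only the planned inference is unsuited to the objective.

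**What to change.** In the main trial's Statistics section:

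- Make the primary result the number of participants with a 4-hour WBC below the lower reference limit (3.5 × 10⁹/l) over the number treated, with an exact (Clopper-Pearson) 95% confidence interval.
- State in advance that 0/14 would leave true rates up to 23.2% compatible, and that a true 10% rate gives 0/14 with probability 23%.
- Report changes in WBC, other laboratory values and vital signs as paired differences with 95% confidence intervals, labelled descriptive.
- Drop p<0.05 as evidence for or against safety.

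In the Summary, reword the objective as estimating the rate of the defined toxic effect. Word the conclusion after 0/14 as no toxic effect observed, with rates above the upper limit excluded, instead of safe. If events occur, give the observed proportion with its interval.

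The cost is wording only: participants, procedures and data collection do not change. The downside is a more modest headline claim.
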